### Study design

This study is a prospective, multicenter, triple-arm, parallel-group, crossover, randomized, controlled clinical trial. The crossover design serves the purpose of analyzing, in an exploratory form, the secondary endpoints (g) and (h), but does not contribute to the power of the primary endpoint analysis. The reason is that a meaningful crossover analysis would have necessitated that patients revert back to fluid overload, prior to their entering into a new treatment phase; a procedure that we considered unethical.

### Study setting and organizational details

Patient recruitment and follow-up are conducted at the maintenance hemodialysis facilities of the Medical University of Vienna, the Sozialmedizinisches Zentrum Süd in Vienna and the Krankenhaus Donauspital SMZ Ost in Vienna. Baseline demographics from the Medical University of Vienna hemodialysis facility [49] compare very well to international dialysis demographics, as in our recent analysis using data from the Dialysis Outcomes and Practice Patterns study (DOPPS) [50]. Demographics from the other two hemodialysis facilities are not available prior to the start of this study.

The study flow chart is depicted in Figure 1. The inclusion criteria are (1) hemodialysis vintage >3 months, (2) fluid overload ≥15% ECW predialysis, as determined by BCM measurement, after one of the two midweek interdialytic intervals, and (3) informed consent of the patient. There are no specific exclusion criteria, other than the reciprocal inclusion criteria, and those criteria implied by good clinical practice and the Declaration of Helsinki (for example, exclusion of minors and of mentally disabled patients). Patients will only be included once. Monitoring of the participants will be ended after the participants’ completion of the study phases.

**Figure 1 F1:**
[figure not shown]
**Study flow chart.** The duration of the crossover period will depend on the run-in phase required for the next study arm: up to six hemodialysis sessions for regulation of ultrafiltration and temperature (UTR), and up to twelve hemodialysis sessions for regulation of ultrafiltration and dialysate conductivity (UCR), no run-in required for conventional hemodialysis. BCM, body composition monitor; ECW, extracellular water.

For patients who are willing to participate in the study, dry weight reduction is prescribed according to a previously published algorithm [11] described here below. Block randomization takes place in a 1:1:1 ratio into study group A (UCR), study group B (UTR) or study group C (conventional hemodialysis). The randomization code is developed using an internet-based randomization tool [51] and is not revealed to participants or investigators. We are stratifying by hemodialysis center, thus there is a different randomization list for each center.

UCR and UTR cannot be applied without previous knowledge of a particular patient’s blood volume changes during the hemodialysis session, which have been shown to be variable, intra- and inter-individually [25]. Therefore, UCR and UTR require a run-in period, which has to be performed every time that UCR and/or UTR are being used. Completion of the run-in period is judged successful for UCR, respectively UTR, if the responsible technicians from Nikkiso, respectively Fresenius, have set the blood volume corridors, respectively have determined the critical point, for adequate use of UCR, respectively UTR. No more than a maximum of twelve, respectively six, hemodialysis sessions are provided to the Nikkiso, respectively Fresenius, technicians, as previously agreed.

Baseline is defined as the day of the BCM measurement. Time zero is defined, for every study phase, as the first hemodialysis session with dry weight reduction after the run-in phase. After completion of the first study period (twelve hemodialysis sessions for all three groups), patients crossover to the respective other study arms, as prespecified at the time of randomization. There is no explicit washout period between the first study phase and any of the subsequent study phases. However, another run-in period is required for the nonconventional treatment arms, before study phases 2 and 3. BCM measurements to adjust or re-prescribe dry weight reduction will be performed before every run-in period, and shortly before time zero of every study phase. If there is reason to believe that patients may have a change in their dry mass during the study period (for example, patients who are hospitalized or who change their diet), BCM measurement will be repeated, and the dry weight adjusted accordingly.

### Study interventions

This study does not interfere with the principle of best practice hemodialysis treatment, which has been described elsewhere [52]. Patients with hemodiafiltration protocols who agree to participate are switched to hemodialysis for the duration of the study.

#### Dry weight reduction

The BCM measurement for fluid overload is provided in kilograms and percentage of ECW. A patient’s new dry weight is calculated as follows: (Predialysis body weight – (fluid overload + 7% ECW)). Thus it is the normohydration weight −7% ECW, and serves as the new, BCM- determined, ideal, or ‘final’ dry weight. In order to reach this ‘final’ dry weight, the patient’s previous dry weight is decreased as previously described in the ‘Dry-Weight Reduction in Hypertensive Hemodialysis Patients’ (DRIP) trial [11]: by 0.1 kg per 10 kg body weight at every hemodialysis session until the final dry weight is reached or any intradialytic complications (listed in Table1) may occur.

An exemplary dry weight reduction scenario is provided in Figure 2. In the event of the first intradialytic complication, standardized clinical interventions take place as listed in Table2, and the dry weight of the ongoing hemodialysis session is re-adjusted to the dry weight of the previous hemodialysis session. At the subsequent hemodialysis session, the dry weight is prescribed as 50% of the previous, additional fluid removal, and all further dry weight reductions are prescribed accordingly. In the event of the second intradialytic complication, standardized clinical interventions take place, and the dry weight at the ongoing hemodialysis session is re-adjusted to the dry weight of the previous hemodialysis session, as before. At the subsequent hemodialysis session, fluid removal is further reduced by 50% of the corrected, additional fluid removal, or to a minimum of 200 g (whatever occurs first, depending on the overall weight of the patient). In the event of a third intradialytic complication, standardized clinical interventions take place, and the dry weight at the ongoing hemodialysis session is re-adjusted to the dry weight of the previous hemodialysis session, as before. No further attempts are made to reduce the dry weight during this study period, unless the patient did not yet reach reduction steps of 200 g.

**Figure 2 F2:**
[figure not shown]
An exemplary dry weight reduction scenario.

**Table 2 T2:** Clinical interventions

	**1**^**st**^**intervention**	**2**^**nd**^**intervention**	**3**^**rd**^**intervention**	**4**^**th**^**intervention**
Cramping	20 mL NaCl (1 M)*	according to doctor's order		
Nausea	Trendelenburg position	250 mL NaCl (0.9%)	plasma expander	according to doctor's order
Vomiting				
Clinically symptomatic IDH				
Decrease in intradialytic SBP ≥40 mmHg				
Unspecified	according to doctor's order			

*5.85% weight/volume. *IDH* intradialytic hypotension, *M* molar, *NaC1* sodium chloride, *SBP* systolic blood pressure.

At the occurrence of symptoms, ultrafiltration is decreased and dry weight adapted, as per the study’s protocol.

Justification for the duration of the study phase: 12 hemodialysis sessions per study phase imply that, if regulated ultrafiltration can prevent intra- and post-dialytic complications, a 70 kg patient is, in theory, able to remove as much as 12 × 700 g = 8.2 L of excess fluid within one study phase. Therefore, we expect that for the great majority of patients, we would theoretically be capable of removing all excess fluid within one study phase.

#### UCR and UTR versus conventional hemodialysis

The principle difference between the two techniques under investigation, UCR and UTR, in comparison to the standard treatment (conventional hemodialysis), is that the ultrafiltration rates in the UCR and UTR groups are variable, and - usually - increased at the beginning of the dialysis treatment, when blood volume slopes are flatter, indicating that refilling takes place from the interstitial to the intravascular compartment. By contrast, ultrafiltration rates in the conventional hemodialysis group are constant, and can be calculated by dividing the total amount of ultrafiltration by the dialysis treatment time.

UCR: dialysis machines from Nikkiso which allow UCR are currently in use at all three participating centers. After recording several (up to 12) hemodialysis sessions, an individual BVM reference corridor - above and below the typical blood volume slope - is determined for every patient. Ultrafiltration as well as dialysate conductivity regulation are started from there on until the end of this study period. In addition to variable ultrafiltration rates, the conductivity component of UCR - through intradialytic changes in dialysate sodium - is aimed at further increasing the refilling process, whenever blood volume slopes indicate that this is necessary.

UTR: dialysis machines from Fresenius which allow UTR are currently in use at all three participating centers. After recording several (up to six) hemodialysis sessions, the ‘critical point’ (the lowest point of the BVM curve) is determined. Above this point, the machine may increase ultrafiltration rates during the beginning of the hemodia-lysis session (as by the inbuilt ultrafiltration regulation device). When the critical point is approached, the machine decreases ultrafiltration rates, to avoid intradialytic complications. Ultrafiltration and temperature regulation (by activating the BTM in the temperature control mode) is started from there on until the end of this study period. The temperature component of UTR is aimed at keeping the body temperature constant, and thereby thought to increase intradialytic stability by preventing overheating and thus vasodilation.

Conventional hemodialysis: in the conventional dialysis arm, we do not allow changes in dialysate temperature, but continue with the dialysate temperature of the patient’s last treatment. We also do not allow changes in the DNa prescription from the patient’s last treatment and changes in other aspects of the dialysate fluid composition (this also applies to the UCR and UTR study arms).

Other than ‘intelligent’ regulation of ultrafiltration, the potential advantage of UCR and/or UTR over conventional hemodialysis is that the dialysis machine alarm goes off in the case that the blood volume slope of the patient during a regulated treatment approaches the corridors (UCR/critical points (UTR)) set for that patient. The dialysis nurse then has the possibility to overrule this alarm, or to decrease and/or interrupt the total ultrafiltration prescribed for that particular treatment. Since the aim of UCR and UTR is to decrease dialysis complications, nurses are instructed never to overrule an alarm, but to decrease and/or interrupt the prescribed ultrafiltration.

#### Antihypertensives

Antihypertensives are withdrawn as in a previous study on dry weight reduction [11], starting one week prior to the first hemodialysis session with reduced dry weight. Alpha and beta blockers are withdrawn first, followed by calcium channel blockers and blockers of the renin-angiotensin-aldosterone system last. The accepted systolic blood pressure during the course of the patient’s antihypertensives withdrawal phase shall generally not surpass 200 mmHg.

### Data retrieval and data recording

Intra- and post-dialytic complications (primary outcome parameter) as specified in Table1 are recorded on the patient’s case report form, and filled out at every hemodialysis session. Secondary outcome parameters: the body weight reached at the end of every hemodialysis session is recorded in the patient’s case report form. Residual renal function is assessed by measurements of 24-hour urine. Quality of life forms are kept in paper format and analyzed using MS Excel 2003. All nonexperimental laboratory data are extracted from the patients’ hospital records and analyzed separately from the dialysis-related outcomes using MS Excel 2003.

### Definition of intradialytic and postdialytic complications

The list of intradialytic complications was chosen in close analogy to a list of secondary outcome measures in the CLIMB study (Table 4 in [20]), and to the DRIP trial (Supplementary Table1 in [11]). As an operational defi-nition of what is ‘clinically symptomatic’, we specify that, nausea, dizziness, vomiting, or any other symptom that the patient may report, if it is most likely related to fluid withdrawal, shall be judged as ‘clinically symptomatic’. Based on our dialysis experience and using the DRIP trial reports as a basis [11], we preclude that besides cramping, intradialytic hypotension is the major obstacle in intensified fluid withdrawal, since hospitalizations - also related to vascular access problems - are dealt with in the analysis of serious adverse events. There are no measurements taken against intradialytic hypertension during the course of the study, unless specifically ordered by the responsible physicians, based on individual patient needs.

### Informed consent

The investigator explains the nature of the study, its purpose, procedures, expected duration, and the potential risks and benefits associated with study participation along with any discomfort that may be expected. Patients are informed about the strict confidentiality of their subject data, but also that their medical records may be reviewed for trial purposes by authorized individuals other than their treating physician. Each subject is informed that study participation is voluntary and withdrawal is possible at any time during the study period. Withdrawal does not prejudice the subject’s subsequent care. Subjects are given time to read and understand the statements before signing consent and dating the document. Subjects receive a copy of the signed written statement and the original copy of the informed consent is stored in the investigator study files. No subject is entered into the study until informed consent has been obtained.

### Safety assessments

Safety assessments include the monitoring and recording of all adverse events (AE), including serious adverse events (SAE). An AE is any undesirable experience associated with the use of a medical product or procedure in a patient. An SAE is defined as any untoward medical occurrence that, at any dose, results in death, is life-threatening, requires inpatient hospitalization or prolongation of existing hospitalization, or results in persistent or significant disability/incapacity. The most probable AEs caused by dry weight reduction are cramps and hypotension. The expected intra- and post-dialytic symptoms are provided in Table1. The most probable serious adverse events caused by dry weight reduction are vascular-access-related hospitalizations, and aggravated consequences of postdialysis hypotension, such as fractures due to falling.

### Quality control

Execution of the three techniques under investigation is crucial. Evaluation of the success of UCR and UTR will be evaluated at the end of the first study phase for all available treatments and will include at least the following parameters:

Availability of a reference line for the setting of corridors (UCR) critical values (UTR) during the run-in phase. Specifically, the number of treatments during the run-in phase with an available reference line will be reported per patient, and per all of the treatments during the run-in phase.

Delayed start of UCR/UTR during the study phases. Specifically, the number of treatments during the study phase with a delayed start (>10 minutes) of UCR/UTR will be reported per patient, and per all of the treatments during the study phase.

Delayed input of the ultrafiltration goal during the study phase. Specifically, the number of treatments during the study phase with a delayed input of the ultrafiltration goal (>10 minutes) will be reported per patient, and per all of the treatments during the study phase.

Incorrect input of the ultrafiltration goal during the study phase. Specifically, the number of treatments during the study phase with an incorrect input of the ultrafiltration goal will be reported per patient, and per all of the treatments during the study phase.

Inadequate display of the ultrafiltration rate and conductivity during the study phase. Specifically, the number of treatments during the study phase with an inadequate display of the ultrafiltration rate and conductivity during the study phase will be reported per patient, and per all of the treatments during the study phase.

### Statistical analysis plan

The statistical analysis plan (SAP) provides full details regarding the analyses, the data display, and the algorithms to be used for data derivations. The SAP includes the definition of major and minor protocol deviations, which will be identified by medically trained staff before the study closure. Safety and tolerability are analyzed descriptively. Safety analysis is performed on the intention-to-treat (ITT) population. All secondary endpoint analyses are exploratory in nature.

Sample size calculation: for the primary endpoint analysis, we will assess the differences in intradialytic complications between the three study groups, only during the first study phase. Based on a typical occurrence of 0.14 dialysis-related complications per patient-day at risk in the conventional hemodialysis group [20], two-sided testing and an expected standard deviation of 10%, an alpha = 0.05 and a beta = 0.2, a sample size of 17 patients per group was determined to detect a minimum difference of 10% between groups. The UCR and UTR groups will be tested against the conventional hemodialysis control group, and afterward against one another. We expect a drop-out rate of approximately 10%. Individuals who do not complete the study cannot be replaced, because we do not include patients with hemodialysis vintage <3 months, and all patients who qualify for the study are asked to participate after the initial BCM measurement at all three centers. Thus, the study sample was determined to consist of 60 patients with ECW ≥15%, by BCM measurement. If patients are lost to follow-up, they will be excluded from the analysis

Two different analysis sets are defined for safety and efficacy, respectively. The efficacy of UCR and UTR will be assessed in all subjects who received the study method (at least once) and did not violate the protocol in a way that might affect the evaluation of the effect of the study method on the primary objective, that is, without major protocol violations. The per-protocol set is employed in the analysis of efficacy variables. The safety analysis set includes subjects who were randomized and received at least one study method (modified intention-to-treat). The safety set is employed in the analysis of tolerability and safety variables. Statistical analysis is performed with SAS.

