### Objectives and outcome measures

The primary objective is to demonstrate superiority of ultrafiltration and dialysate conductivity regulation (UCR) and/or ultrafiltration and temperature regulation (UTR) over conventional hemodialysis, in preventing intra- and post-dialytic complications, when fluid-overloaded hemodialysis patients receive systematic fluid reduction, to reach a final dry weight of normohydration weight −7% of ECW postdialysis. The primary outcome measure is the total number of hemodialysis sessions per patient that were accompanied, intra- or post-dialytically, by at least one symptom most likely related to fluid withdrawal (as specified in Table1), divided by the number of hemodialysis sessions at risk (as by study protocol: 12 sessions per patient in study phase 1). Both groups, UCR and UTR, will be compared against the conventional hemodialysis group, and afterward against one another, using the two-sided Student’s *t* test

**Table 1 T1:** Complications related to fluid withdrawa

(1)	Intradialytic cramping
(2)	Intradialytic hypotension (>40 mmHg SBP) within 30 minutes: clinically asymptomatic
(3)	Intradialytic hypotension (>40 mmHg SBP) within 30 minutes: clinically symptomatic
(4)	Clinically symptomatic intradialytic hypotension: unspecified drop in SBP
(5)	Unspecified intradialytic complication, most likely related to fluid withdrawal
(6)	Patient-reported postdialysis complication, most likely related to fluid withdrawal

The secondary objectives are:

(a). To demonstrate superiority of ultrafiltration and dialysate conductivity regulation (UCR) and/or ultrafiltration and temperature regulation (UTR) over conventional hemodialysis, in preventing specific intradialytic complications:when fluid-overloaded hemodialysis patients receive systematic fluid reduction, to reach a final dry weight of normohydration weight −7% of ECW postdialysis. The secondary outcome measure for objective (a) is the total number of hemodialysis sessions per patient which were accompanied by the respective symptom most likely related to fluid withdrawal (1 to 6), divided by the number of hemodialysis sessions at risk (as by study protocol: 12 sessions per patient in study phase 1). Both groups, UCR and UTR, will be compared against the conventional hemodialysis group, and afterward against one another, using the two-sided Student’s *t* test.

1. intradialytic cramping

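### Efficacy is analysed only per protocol and without patients lost to follow-up, while only UCR and UTR patients must pass a run-in after randomisation, so the superiority comparison is open to selection bias

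*Protocol article*

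**What the plan says.** Under Objectives and outcome measures, the claim is one of superiority: "The primary objective is to demonstrate superiority of ultrafiltration and dialysate conductivity regulation (UCR) and/or ultrafiltration and temperature regulation (UTR) over conventional hemodialysis".

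The Statistical analysis plan section fixes the populations. "Two different analysis sets are defined for safety and efficacy, respectively". For efficacy, "The efficacy of UCR and UTR will be assessed in all subjects who received the study method (at least once") and who had no major protocol violation; then "The per-protocol set is employed in the analysis of efficacy variables". Loss to follow-up is handled by removal: "If patients are lost to follow-up, they will be excluded from the analysis". No efficacy analysis of all randomised patients is named.

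Study setting and organizational details describes the run-in. UCR and UTR need one, and it succeeds if the manufacturers' technicians have been able to set the blood volume corridors or the critical point. "No more than a maximum of twelve, respectively six, hemodialysis sessions are provided to the Nikkiso, respectively Fresenius, technicians, as previously agreed". The Figure 1 legend says that conventional hemodialysis needs none. Time zero of each phase comes after the run-in, and under Study interventions regulation is switched on only once the corridor or critical point is known.

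The safety population is described in two ways in the same section: "Safety analysis is performed on the intention-to-treat (ITT) population", and later "The safety analysis set includes subjects who were randomized and received at least one study method (modified intention-to-treat").

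**The concern.** A superiority claim rests on comparing the groups that randomisation formed. Here membership of the efficacy set depends on events after randomisation, and one of these, the run-in, exists in two arms only. If patients with unstable blood volume curves are the ones for whom no corridor or critical point can be set, or who leave during the run-in, the regulated arms lose patients prone to the very complications that the primary endpoint counts.

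Two features add to the exposure. The trial is unblinded, and the Discussion accepts that this can introduce bias, yet staff decide which deviations are major. Some execution faults listed under Quality control, such as a missing reference line or a late start of UCR or UTR, can occur only in the regulated arms. If they were classed as major, those exclusions would be one-sided as well.

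The loss-to-follow-up sentence is also not limited to phase 1. Read literally, it discards the complete primary data of a patient lost in phase 2 or 3, although the primary endpoint uses phase 1 alone.

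**Working it through.** **1. Who can leave the primary comparison, and where**

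| Step after randomisation | UCR | UTR | Conventional |
|---|---|---|---|
| Run-in before time zero | up to 12 sessions, can fail | up to 6 sessions, can fail | none |
| Antihypertensive withdrawal, from one week before the first reduced dry weight | yes | yes | yes |
| Loss during phase 1 | excluded | excluded | excluded |
| Loss in phase 2 or 3 (literal reading) | excluded | excluded | excluded |

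The run-in depends on the assigned arm, so it must follow randomisation. A patient who does not complete it has not yet had regulated treatment and so does not meet the entry condition for efficacy. Only this row differs between arms.

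**2. The plan's own sample size**

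Inputs (Statistical analysis plan): difference 10 points, SD 10 points, two-sided alpha 0.05, power 80%, dropout about 10%, total 60. The standardised difference is 10/10 = 1. The two-sample t test needs 16.71, so 17 per group, with power 80.7% at 17. The stated figure reproduces. For dropout, 3 × 17 / 0.9 = 56.7, so 57; the plan's 60 is a rounding up. After 10% dropout, 60 × 0.9 / 3 = 18 per arm remain, one above the 17 required. Further per-protocol exclusions have to come out of that margin.

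**3. Possible size of the bias**

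Assumptions not in the article: no true effect; patient-level rates with mean 0.14 (the plan's control rate) and SD 0.10, beta-distributed; 20 per arm; k patients lost from one regulated arm and none from the control arm; two-sided t test; 20,000 simulated trials. Loss is unrelated to the outcome, moderately related (correlation 0.5 on a latent normal scale), or falls on exactly the patients with the highest rates.

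| Lost of 20 | Unrelated | Correlation 0.5 | Exactly the highest |
|---|---|---|---|
| 1 | 0 points, 5.2% | −0.5, 5.4% | −1.2, 7.5% |
| 2 | 0 points, 5.0% | −1.0, 6.2% | −2.2, 11.5% |
| 3 | 0 points, 4.7% | −1.4, 7.0% | −3.0, 17.9% |
| 4 | 0 points, 4.8% | −1.7, 8.1% | −3.7, 24.6% |

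Each cell gives the mean false difference (negative favours the regulated arm) and the two-sided type I error. The row for 2 corresponds to the plan's 10% dropout, placed wholly in one arm.

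**4. What an all-randomised analysis costs in power**

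Assume that a fraction f of a regulated arm never starts the method and has the control rate, with SD still 10 points and 20 per arm. The expected difference becomes 10 × (1 − f) points, so the standardised difference is 1 − f.

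| f | Difference | Power |
|---|---|---|
| 0% | 10.0 | 86.9% |
| 5% | 9.5 | 83.3% |
| 10% | 9.0 | 79.2% |
| 15% | 8.5 | 74.5% |
| 20% | 8.0 | 69.3% |

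**The case against.** A reader might infer that the comparison is already biased, and in favour of UCR and UTR. The article does not support that, for three reasons.

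- The loss-to-follow-up exclusion applies to every arm. If conventional patients have more complications, as the trial hypothesises, removing those who leave for poor tolerance takes high-risk controls out and works against UCR and UTR. Conventional patients can also leave before time zero, during antihypertensive withdrawal.
- The article does not say in words what happens after a failed run-in; exclusion is inferred from the entry condition.
- Nothing links run-in failure to complication risk. Failure may be technical, and the Discussion cites conflicting evidence on whether blood volume curves relate to hypotension at all. If loss is unrelated to risk, there is no bias.

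A larger false effect is also tempting. If the 2 of 20 patients with the highest true risk were lost, with intraclass correlations of 0.05, 0.1 or 0.2 between a patient's sessions, it would be 1.7, 2.5 or 3.7 points. Those correlations imply SDs of 12.5, 14.5 and 17.9 points, not the plan's 10. Binomial variation over 12 sessions alone gives √(0.14 × 0.86 / 12) = 10.0 points. Taken strictly, the plan's SD therefore leaves almost no between-patient differences in risk to select on: at an intraclass correlation of 0.001, the same loss gives 0.2 points.

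These arguments limit direction and size. They do not restore a comparison of the groups as randomised. The full SAP, which is not shown, defines major deviations, but it could not add a different primary efficacy set without contradicting the published section.

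A last objection is that an all-randomised set has no outcome for patients without any phase 1 session. That is right, and the change needs an explicit rule for them.

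**Conclusion.** The concern holds as a risk of bias, not as demonstrated bias. The plan itself fixes a per-protocol set as the only efficacy set for an unblinded superiority claim, removes patients lost to follow-up, and places a run-in that can fail between randomisation and time zero in two of three arms. Selective loss of unstable patients in that run-in would favour UCR and UTR; loss for poor tolerance in phase 1 can occur in any arm and may pull the other way.

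With 2 of 20 lost from one regulated arm, the false benefit ranges from 0 to about 2 points against a 10-point target, and type I error from about 5% to 11.5%. This rests on the assumed SD of 10 points and on loss in one arm only. The upper end also supposes that exactly the patients with the highest rates go. The point should be settled before analysis, because it decides who enters the primary comparison.

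The two descriptions of the safety population are a separate and minor contradiction. Safety is analysed descriptively, and all adverse events are to be recorded.

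**What to change.** 1. Define the primary efficacy set as all randomised patients, analysed in the arm assigned for phase 1 whatever method was delivered. The denominator is the phase 1 sessions at risk actually attended, which fits the endpoint's existing definition as a proportion of sessions at risk.
2. Delete the sentence that excludes patients lost to follow-up. Early leavers, and patients lost only in phase 2 or 3, then keep their phase 1 data.
3. State in advance how failed run-ins are counted. Patients who continue with dry weight reduction are analysed as assigned, with a stated start of phase 1. Patients with no phase 1 session are reported by arm and reason and covered by a sensitivity analysis, for example giving them the control-arm rate and then a worse one. Whether such patients continue is a clinical matter outside this point.
4. Keep the per-protocol analysis as supportive.
5. Reconcile the two safety statements into one set that covers events from randomisation, including the run-in.

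Cost: mainly protocol and SAP wording. Case report forms are already completed at every session, but outcomes must also be recorded for patients who proceed without regulation. The effect may be diluted: with 20 per arm and SD 10 points, power is about 79% if 10% of a regulated arm never start the method, and lower beyond that.
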